## Qualitative measures

While the quantitative data we propose to gather and analyze should provide us with valuable information as to the extent to which the IYP is impacting quality of life and ability to function, qualitative interview data should also serve to elucidate the quantitative data and help us to tease out the nuances of the findings. That is, we expect the semi-structured interviews to yield a rich source of information that provides us with a more comprehensive picture of the issues facing RA patients and the process by which the yoga practice changes their daily lives. Specific topics to be covered will include: the nature of their symptoms and the life domains they affect; how specifically and the extent to which these life domains are impacted; the patients' attempts at self-management of the symptoms; the strength of their social networks and the impact of the symptoms on these networks; and their perceptions of the yoga program. Interviews will be conducted at the end of the intervention by a social scientist experienced in the design, collection, and analysis of qualitative data.

## Data analyses

### Quantitative statistical analysis

After the data have been entered and cleaned, the statistical plan will unfold in two stages. The first stage will involve assessing outcome measures for reliability and general integrity (e.g., distribution characteristics) to ensure that appropriate techniques are applied during data reduction and model testing. The second stage will consist of: 1) descriptive procedures to detail the dataset, and 2) primary analyses to answer the research questions forming the basis of this proposal.

Each stage of data analysis detailed below will initially be carried out separately for younger (16-18 yrs) and older (19-21 yrs) sub-groups. If no differences are found on analyses, the groups will be combined.

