**Methods/Design:**

Seventy rheumatoid arthritis patients aged 16-35 years will be randomized into either the 6-week Iyengar yoga program (12 - 1.5 hour sessions twice weekly) or the 6-week wait-list control condition. A 20% attrition rate is anticipated. The wait-list group will receive the yoga program following completion of the first arm of the study. We will collect data quantitatively, using questionnaires and markers of disease activity, and qualitatively using semi-structured interviews. Assessments include standardized measures of general and arthritis-specific function, pain, mood, and health-related quality of life, as well as qualitative interviews, blood pressure/resting heart rate measurements, a medical exam and the assessment of pro-inflammatory cytokines. Data will be collected three times: before treatment, post-treatment, and two months following the treatment.

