### Design

A randomized control trial (RCT) design will be used to examine the impact of IYP for adolescents and young adults aged 16-35 years with RA on the primary outcomes of general and arthritis-specific functioning, and the secondary outcomes of DAS28, pain and mood.

The overall design of the study is depicted in Figure 2 below. After participants have completed the telephone screening and meet the study's eligibility criteria, they will be randomized into the IYP or usual care control group. All participants will be asked to fill out consent forms before their initial medical assessment, which includes a phlebotomy, measurement of blood pressure/resting heart rate, and a joint count conducted by a physician who will be kept unaware of group assignment. Before the medical assessment, a research assistant will send a link to the questionnaires for participants who choose to complete them online. A hard copy of the questionnaires will be taken to the medical assessment if the participant chooses to complete the paper-based version in a private medical office.

Those assigned to the IYP will then engage in the 6-week program; they will repeat the baseline assessments immediately following treatment and again at a two-month follow-up. Patients initially assigned to the wait-list group will continue their usual care. Both the yoga and control groups will either receive weekly phone calls or e-mails to monitor symptoms, medication use and physical activity. After 6 weeks, control participants will be re-assessed to ensure that they still meet study eligibility criteria; those that continue to meet criteria will then take part in the IYP. Following the IYP, participants will then repeat the baseline assessments at post-treatment and two-month follow-up.

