### Enrollment criteria

Young women and men will be eligible for the study if they meet the following criteria:

• Age 16-35 years.

• Diagnosis of RA, according to the revised 1987 ACR criteria for at least 6 months.

• Concomitant use of disease modifying antirheumatic medications (hydroxychloroquine, sulfasalazine, methotrexate, leflunomide, etc.) and/or biologic agents (infliximab, etanercept, adalimumab, abatacept, rituximab, anakinra) is permitted provided that the dose(s) have been stable for 8 weeks prior to screening, and subjects may reasonably be expected to remain on stable doses throughout the study.

• Concomitant use of NSAIDs and low dose corticosterioids (e.g., prednisone at doses of 10 mg/day prednisone or equivalent) is permitted provided that the dose(s) have been stable for 4 weeks prior to screening, and subjects may be expected to remain on stable doses throughout study duration.

• Disease activity, as defined using a 28 joint count by ≥ 5 tender joints, ≥ 5 swollen joints, and one of the following: Erythrocyte Sedimentation Rate (ESR) ≥ 28 mm/hour, C-reactive protein (CRP) ≥ 1.5 mg/dL, duration of a.m. stiffness ≥ 45 minutes.

• Able and willing to give written informed consent and comply with the requirements of the study.

• Ability to speak and understand English.

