### Recruitment

Participants will be recruited from the UCLA Division of Rheumatology, the UCLA pediatric rheumatology program, private medical offices of rheumatologists, UCLA Student Psychological Services, health newsletter ads, the young adult support network of the Southern California Chapter of the Arthritis Foundation, and community resources, such as library and other public notice boards, as well as websites, such as Craigslist. The UCLA Division of Rheumatology has a current patient population of 150 individuals with RA who are 16-21 years of age. The UCLA pediatric rheumatology program sees 100 patients with arthritis 16 years and older. Private practice rheumatologists in Los Angeles who have agreed to assist with our project can refer an additional 200 patients with RA in our targeted age range. The Southern California chapter of the Arthritis Foundation will help us recruit from their pool of several hundred RA patients who regularly receive their email announcements and mailed bulletins. In all, we anticipate being able to recruit from a pool of over 500 individuals with RA in the targeted age-range.

The project director will meet with health care providers, staff and support group leaders to inform them about the project and to ask them to distribute and post flyers about the study. The flyers will describe the project and ask interested volunteers to call the project manager to establish their eligibility. Additionally, a lay advisory board comprised of young adults with RA will be formed and consulted with in the development of recruitment materials as well as in the finalization of the protocol and research instruments.

Effort will be made to recruit the patient sample to be broadly representative of the general population of RA patients in the targeted age range. Epidemiological data suggest that the racial composition of RA in the U.S. is approximately 84.4% non-Hispanic whites, 8.3% non-Hispanic blacks, 2.3% Mexican American and 5% other [50]. Women are between 60-75% more likely to experience RA than men [50,51]. We will also attempt to recruit patients to reflect the demographic composition of the Greater Los Angeles area which is estimated to be approximately 75% White, 13% Asian, 10% African-American, 1% American Indian/Alaska Native, and 1% Native Hawaiian/Other Pacific Islander; ethnic makeup will be 45% Hispanic and 55% Non-Hispanic.

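### The analysis rule splits the sample into ages 16-18 and 19-21, so enrolled participants aged 22-35 have no place in it, and pooling depends on an undefined finding of no difference

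*Protocol article*

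**What the plan says.** Eligibility is "Age 16-35 years" (Enrollment criteria). The abstract agrees: "Seventy rheumatoid arthritis patients aged 16-35 years will be randomized". So does the Design section, which refers to "adolescents and young adults aged 16-35 years with RA".

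Under Data analyses, Quantitative statistical analysis, the rule is that every stage that follows is at first to be "carried out separately for younger (16-18 yrs) and older (19-21 yrs) sub-groups. If no differences are found on analyses, the groups will be combined". No third band is named, and no test, outcome or threshold is given for deciding that there are no differences.

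Two other places bear on this. The sample size section derives one total of 54 (27 per group) for the treatment-by-time interaction, with 35 per group recruited to allow for 20% attrition. Primary analyses adds an intent-to-treat analysis of the primary outcomes that takes in everyone who enrolled.

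**The concern.** The rule governs every stage after it, including the primary comparison on the SF-36, PDI and HAQ. Its two bands end at age 21, and so does their union. A participant aged 22-35 is eligible and randomised, yet the rule assigns that person to no analysis. An analyst would have to leave such participants out or invent a grouping once data are in hand.

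A second defect does not depend on where the bands end. The rule runs the randomised comparison on the whole sample only if the age bands show no difference. What the trial reports as its main result would then depend on a look at the data, in strata for which the trial was not sized.

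**Working it through.** **Age coverage.** Eligible single years of age: 35 − 16 + 1 = 20. Years in the two bands: 21 − 16 + 1 = 6. Years in no band: 20 − 6 = 14 (ages 22-35), which is 14/20 = 70% of the age span. This is a share of the age range, not of patients; the article gives no age distribution.

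**The plan's own sample size.** The pre-post correlation ρ is not stated, so 54 cannot be strictly reproduced, but it is attainable. For a 2 × 2 repeated-measures interaction, λ = f² × N × 2 / (1 − ρ). With f = 0.46/2 = 0.23 and an assumed ρ = 0.30, λ = 0.0529 × 54 × 2 / 0.70 = 8.16, and power is 0.80. For attrition, 27/0.80 = 33.75, so 34 per group; the plan recruits 35 and expects 35 × 0.80 = 28 completers per group, 56 in all. These figures are for one undivided sample.

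**If only ages 16-21 were analysed.** The same formula is used with 56 completers and an assumed share aged 16-21:

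| Assumed share aged 16-21 | Number analysed | Power |
|---|---|---|
| 30% | about 16 | 0.31 |
| 50% | 28 | 0.51 |
| 80% | about 44 | 0.71 |
| 100% | 56 | 0.82 |

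**What a finding of no difference can show.** Take the case kindest to the rule: all 56 completers fall in the bands and split equally, giving 14 per arm in each stratum. Let the treatment effect differ between strata by d = 0.5 (in units of the baseline SD). Assume ρ from 0.5 to 0.8 and a two-sided test at 0.05.

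- SD of change = √(2(1 − ρ)): 1.00 at ρ = 0.5 and 0.632 at ρ = 0.8.
- SE of the difference between the two stratum effects = SD × √(4/14): 0.535 and 0.338.
- Non-centrality = 0.5/SE: 0.94 and 1.48, on 4 × 14 − 4 = 52 degrees of freedom.
- Power: about 0.15 and 0.31.

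A true difference of that size would be missed about 69% to 85% of the time.

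**A chance difference.** If the unstated criterion were a test at 0.05 on each of the three primary outcomes (an assumption), the chance that at least one shows a difference when none exists is 1 − 0.95³ = 0.14 for independent outcomes. It is less for correlated outcomes, down to 0.05 if they moved together completely. On such a result the rule would not combine the data.

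**The case against.** The strongest defence is that the authors plainly meant to analyse everyone. The intent-to-treat analysis includes all who enrolled, and the sample size treats the trial as one sample. On this view the bands are a stale detail. As an account of intent, this is probably right. It does not settle the text: the intent-to-treat analysis is itself one of the stages placed under the rule, and it is presented as confirming the result in completers. The sections still contradict each other.

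A reader might infer several stronger things, which the documents do not support.

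- *That most of the randomised sample would be lost.* That needs an age distribution, and none is given. Several recruitment sources lean young. Only the share of the age span is known.
- *That the plan treats non-significance as proof that the bands are alike.* The text names no test. The fair criticism is that the condition is undefined and depends on the data. The choice of test might sit in an analysis plan that is not shown, but that would not supply a place for ages 22-35.
- *That the low power for a treatment effect within one small band measures the weakness of the pooling condition.* It answers a different question. The relevant power is for a difference in effect between bands, as calculated above, and it is lower still.
- *That the Recruitment section repeats the error.* Its "current patient population of 150 individuals with RA who are 16-21 years of age" describes one clinic and lies within 16-35. It hints at a narrower age range in the plan's history, but it is not wrong.

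**Conclusion.** The rule is wrong as written and should be corrected before analysis. Participants aged 22-35, who span 14 of the 20 eligible years of age, have no defined place in the separate or the combined analyses. This follows from the text alone and matters as soon as one such person enrols. That the bands are left over from a narrower age range is an inference, and the finding does not rest on it.

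Replacing 21 by 35 would mend the coverage but not the pooling condition. With power of about 0.15 to 0.31 in the most favourable split, a finding of no difference says little, and a chance difference could block the analysis for which the trial was sized. Those figures assume equal strata, an effect difference of d = 0.5 and a pre-post correlation of 0.5 to 0.8. Smaller or unequal strata would lower them.

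**What to change.** Delete the two-sub-group rule from Quantitative statistical analysis. State in its place that all randomised participants aged 16-35 are analysed together in the primary and secondary comparisons. If an age analysis is wanted, let it cover the full 16-35 range and label it exploratory, for example an age-by-group interaction with its confidence interval. State that it does not decide whether data are pooled.

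Age as a covariate is optional. The clinic count under Recruitment needs no change. The cost is the wording of one paragraph, with no effect on recruitment, assessments or sample size.

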### Preliminary analyses

Once the data set has been cleaned and examined for skewness and missing data, exploratory data analyses will be conducted using univariate methods to describe the variables of interest and bivariate techniques to characterize their interrelationships within our sample. Continuous variables will be summarized over time in each group using means and medians and we will also report their range, interquartile range and standard deviations. Cross tabulated frequencies will be given for all discrete variables by group and time. Results from these descriptive analyses will be used to guide the primary analyses by providing information about potential problem measures (e.g., heavily skewed distributions) or problematic variable relationships (e.g., highly correlated predictors) and will help determine if transformations of some outcomes are possible in order to use parametric methods. We will test for baseline between-group differences in the outcome measures. Any variables found to vary significantly by group will be included as covariates in primary and secondary analyses. This will also serve to verify that the randomization was successful.

Missing data will be handled using multiple imputation [74] using the SAS routines PROC MI (20 imputations) and PROC MIANALYZE (to combine estimates). The imputation process is fostered by including additional variables (not part of the intended analytic model) that are highly correlated with variables that have missing data or that are associated with the probability that those variables have missing data. Such covariates (used in imputation only) will vary from analysis to analysis and their viability will be evaluated by preliminary analysis (e.g., zero-order correlations with variables with missing data) and their impact on the imputation model (e.g., change in standard errors of imputed variables). Multiple imputation has been shown to perform well with small samples [74].

For ***Hypothesis 1***: The IYP will be safe, acceptable and feasible: more than 80% of subjects will complete the training program, we will examine the frequencies of drop-outs for the IYP and control groups. We will compare attrition rates between the groups; we will also compare demographic characteristics and baseline values of functioning between those who complete the protocol and those who do not. If drop-outs are random, then the results may be considered unbiased. If drop-outs are not random, we will comment on the direction and magnitude of potential biases.

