#### The hypotheses to be tested are

**1**: The IYP will be safe, acceptable and feasible: at least 80% of subjects will complete the IYP.

**2**: Following the IYP, participants will show significant improvement on the primary outcomes of general functioning, arthritis functioning and HRQOL relative to controls. The benefits will be apparent post-treatment and at two-month follow-up.

**3**: Following the IYP, participants will report significant improvement on the secondary outcomes of pain, DAS28, and mood compared to controls. These improvements will be evident at both post-treatment and at two-month follow-up.

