#### Phase two (3 Months)

We will further develop the protocol by conducting an initial IY group. We will also train an additional experienced IY instructor and two assistant instructors. The two IY teachers, with their assistants, will teach a small class of 3 AYA RA patients each (total n = 6) to refine the protocol. The purpose of the assistant instructors is threefold: to promote class safety by assisting patients safely in and out of poses and to record adverse events to bring to the attention of the Safety Board (described below); to take class attendance for determination of patient adherence; and to record the poses and modifications used in each class to be evaluated by the Board (described below) for teacher adherence to the core set of poses. The assistants will note for each student: which poses were performed, which props were used, and any difficulties experienced. Weekly team meetings chaired by the PI will be conducted to solicit suggestions on additional refinements to the protocol.

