**Figure 3 F3:**
[figure not shown]
**Selected yoga poses**.

Yoga taught in the Iyengar tradition is known for an extensive teacher training program. Iyengar teachers study for at least seven years before being certified to work with students who have therapeutic needs. They must pass several certification tests before an impartial national board. These tests include teaching, performance of poses and breathing techniques, anatomy and therapeutic sequences. Because of this training, IY teachers across the country and around the world can accurately reproduce the IYP in this study.

The proposed IYP will be administered twice a week for 1.5 hours duration per session for 6 weeks. Due to the extensive time commitment required for the IYP, there will be no instructions for home practice, but neither will participants be discouraged from practicing at home. At the end of the 6-week IYP, those participants who ask for referrals to IY studios/teachers in the community will be given a list of referrals. All home practice as well as post-IYP yoga classes will be monitored during the weekly phone calls/e-mails and at the post-treatment and follow-up assessments; the extent of home practice will be evaluated in the analyses for its potential impact on outcome.

Should subjects experience a flare-up during the IYP, the research team will consult with the patient's rheumatologist and a modified version of the IYP will be offered to the subject consisting of restorative poses that do not place strain on the affected joints.

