## Discussion

Young people with chronic, disabling RA symptoms represent a significantly underserved population. The overarching goal of this project is to develop and test a novel prevention and risk reduction approach to improving functioning and enhancing the quality of life for this population. The data from this project will inform a larger study to conduct a more formalized and advanced trial to further evaluate the utility of IY for improving pain and functionality among RA patients. Ultimately, by amassing a strong evidence base, our IY treatment protocol may eventually become integrated into the established prevention and treatment approach for RA as well as the management of other chronic and debilitating conditions.

A number of limitations may pose challenges to carrying out the proposed study. Given that RA is more typically diagnosed in older adults, recruiting participants who meet our age criteria may prove difficult. It is possible that attrition rates will be higher than predicted. A significantly greater drop-out rate would contradict our hypothesis about feasibility and this finding would force us to reconsider our design. Another potential study limitation is possible difficulties in scheduling the IYP sessions to avoid conflict with school or work and childcare issues. Classes will be scheduled on weekends and evenings at times when the majority of participants are available to address this potential difficulty. Participants will also have the opportunity to attend one make-up session if they miss any regular group classes. Another potential limitation will be the development of an arthritic flare during the IYP or control period. If a participant develops a flare, he or she will be instructed to communicate with his or her treating rheumatologist. The principal investigator will set up a meeting with the Data and Safety Monitoring Committee, which includes a rheumatologist. The Committee will develop a modified treatment plan so that the participant can remain in the IYP and continue with the program using modified poses.

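### Hypothesis 1 concludes that the yoga programme is safe from an 80% completion criterion, which flares need not lower because flaring participants are offered a modified programme so that they can stay

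*Protocol article*

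**What the plan says.** The hypothesis is stated under the heading on hypotheses to be tested: "The IYP will be safe, acceptable and feasible: at least 80% of subjects will complete the IYP". The Preliminary analyses section restates it with a different threshold and names the analysis: "The IYP will be safe, acceptable and feasible: more than 80% of subjects will complete the training program, we will examine the frequencies of drop-outs". That section adds a comparison of attrition between groups and a baseline comparison of completers with non-completers. Nothing else feeds Hypothesis 1.

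Two places deal with flares. In the Intervention section, for a flare during the programme, "the research team will consult with the patient's rheumatologist and a modified version of the IYP will be offered to the subject". The Discussion covers "the development of an arthritic flare during the IYP or control period". There the participant is told to contact the treating rheumatologist, and the principal investigator convenes a Data and Safety Monitoring Committee: "The Committee will develop a modified treatment plan so that the participant can remain in the IYP and continue with the program using modified poses".

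On capturing events, the Phase two section gives the assistant instructors the task "to record adverse events to bring to the attention of the Safety Board". The Design, Usual care control and Exploratory variables sections describe weekly contact in both arms. The listed content of the weekly form is functioning, mood, pain, fatigue, improvement, activity, home practice and medication. The section on the yoga safety and adherence monitoring board says that it reviews safety reports that include adverse events, without giving their source or a breakdown by arm.

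**The concern.** Completion can stand for feasibility and, with some goodwill, for acceptability. It does not measure harm. A participant can be injured or flare and still finish, and another can leave because of work or childcare without any harm at all. The flare provisions loosen the link further, because they are meant to turn a possible drop-out into a completer. That may be sound clinical practice, and no view is taken on it here, but it means that retention cannot also serve as the evidence of safety.

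The Rationale lists safety among the things on which this pilot should inform a larger trial. Entrants must have active disease, so some flares can be expected in both arms. Without a count made the same way in each arm, a flare in the yoga arm cannot be told from an ordinary flare of the disease. Read literally, Hypothesis 1 would let the authors report the programme as safe without having looked at either count.

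**Working it through.** **The plan's own figure.** The enrolment text and the sample size section give 35 recruits per arm and 20% attrition: 35 × (1 − 0.20) = 28, the stated number of completers. Since 28/35 = 80% exactly, the planned result sits on the pass mark.

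**Threshold wording.** Under the at-least-80% wording, 28 of 35 passes; under the more-than-80% wording, 29 are needed. With true completion of 80%, as planned:
- P(X ≥ 28), X ~ Bin(35, 0.80) = 0.60
- P(X ≥ 29) = 0.43

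**Does the criterion respond to flares?** Assumptions, none of them given in the documents:
- d = 0.10, drop-out for reasons other than flare
- q = proportion who flare, from 10% to 50%
- r = share of flaring participants who leave despite the offer, from 0 to 100%
- the 35 initially randomised to yoga are the denominator, and modified-programme participants count as completers

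True completion is c = (1 − d)(1 − q·r), and the chance of passing is the upper binomial tail with n = 35.

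| q | r | c | P(≥ 28 of 35) | P(≥ 29 of 35) |
|---|---|---|---|---|
| 10% | 0 | 0.90 | 0.98 | 0.945 |
| 50% | 0 | 0.90 | 0.98 | 0.945 |
| 10% | 50% | 0.855 | 0.875 | 0.763 |
| 30% | 25% | 0.8325 | 0.78 | 0.63 |
| 30% | 50% | 0.765 | 0.40 | 0.25 |
| 30% | 100% | 0.63 | 0.025 | 0.009 |
| 50% | 50% | 0.675 | 0.08 | 0.03 |

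With r = 0 the term q·r vanishes, so the result is the same at every flare rate. With r above 0 the criterion reacts, but to people leaving, not to flares as such. Injuries among people who finish are likewise invisible to it.

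**What a direct comparison could show.** With 35 per arm, power to separate assumed flare rates is 21% for 10% vs 20%, 55% for 10% vs 30% and 84% for 10% vs 40%. A comparison by arm would therefore be mainly descriptive. With no events in 35, the one-sided 95% upper bound is 1 − 0.05^(1/35) = 8.2%.

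**The two flare passages side by side.** In the Intervention section the research team consults the rheumatologist, and the setting is the yoga programme. In the Discussion the participant contacts the rheumatologist, a committee draws up the modified plan, and control-period flares are named as well, although the outcome described applies to someone in the programme. Neither passage says whether a person on the modified programme counts as a completer for Hypothesis 1.

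**The case against.** The strongest reply is that safety is watched in several ways outside Hypothesis 1. Symptoms and medication are followed weekly in both arms, flares in either period are escalated, and a board sees safety reports. DAS28 is compared with controls under Hypothesis 3, with the joint count made by a physician unaware of allocation. This is also a preliminary pilot, and adverse-event tables are commonly left to an analysis plan that is not shown here. All of that is fair, and it limits the severity. It does not answer the point, because the document states what the safety conclusion rests on, and none of these sources is part of it. Worsening on DAS28 would appear only as a failed efficacy hypothesis.

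Some stronger readings are tempting but not supported:
- A reader might infer that adverse events are recorded only in class. The class assistants are the only recorders named, but the article does not say that they are the only route.
- A reader might take flare to be the main expected harm. The section on protection against risks gives that place to musculoskeletal strain or injury; the Discussion lists flare as a potential limitation. Completion measures neither.
- A reader might place safety in Aim 1. That aim covers feasibility only; safety stands in Hypothesis 1 and the Rationale.
- A reader might conclude that a programme that provokes flares is bound to pass. The modified programme is only offered, and the table shows the chance falling steeply once many flaring participants leave.
- The 8.2% bound is a property of any arm of 35 and no defect of this plan. If all 70 came to receive yoga without an event, it would be 4.2%.

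The two flare passages could also be read as complementary steps. Even so, they differ in who makes contact, who decides and which period is covered.

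**Conclusion.** The point holds in this form: Hypothesis 1 ties the word safe to an 80% completion rule that is analysed only through drop-out, and the plan's own flare provisions make completion a poor measure of harm. If flaring participants accept the modification and other drop-out is 10%, the chance of reaching 28 of 35 is about 0.98 at any flare rate. At an assumed 30% flare rate it drops to 0.78 if a quarter of those who flare leave, 0.40 if half leave and 0.025 if all leave. The flare rates, the 10% and the shares leaving are assumptions. That no event count enters the criterion does not depend on them. No equal adverse-event capture by arm is described and none is linked to the safety conclusion. This should be fixed, but given the pilot setting and the other monitoring it is not a fatal flaw.

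**What to change.** - In the hypotheses section and in Preliminary analyses, separate safety from completion, and keep the 80% criterion for feasibility.
- Base safety on the proportion with at least one adverse event (including musculoskeletal injury) and the proportion with at least one flare, by arm over the randomised 6 weeks, reported descriptively with confidence intervals.
- Collect both through one identical question on the weekly monitoring form already used in both arms, and keep the class logs as a yoga-only listing.
- Report completion of the standard and of the modified programme separately.
- Use one threshold wording, at least 80% or more than 80%, since 28 of 35 passes one and fails the other.
- Reconcile the flare passages in the Intervention and Discussion sections. How flares should be managed is for the investigators.

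The cost is one form item, one table and some rewording. Completion of the standard programme may look less favourable once modified participants are shown separately.
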